### **11.5.2 Amendments of protocol**

Neither the investigator nor the sponsor may alter this trial protocol without obtaining the written agreement of the other party. Subsequent changes to the protocol during an ongoing trial have to be implemented via protocol amendments. The sponsor is responsible for obtaining the approval for the amendments by the ethics committee and/or by the competent authority depending on the provisions of § 10, section 1 GCP regulation.

## **11.6 Other information to ethics committees and competent authorities**

The sponsor is responsible for the ongoing evaluation of the safety of the IMP and the participants of the trial; the corresponding notifications in accordance with § 11 and § 13 GCP regulation are described in chapter 7 ("Safety").

## **11.7 Documentation of Correspondence**

Relevant correspondence with competent authorities and ethics committees will be properly archived by the sponsor or IZKS Mainz on behalf of the sponsor.

## **11.8 Data monitoring committee (DMC)**

The independent data safety and monitoring board (DSMB) will supervise the conduct of this trial and will issue recommendations for early termination, modifications, or continuation of the trial according to the DSMB operating procedure.

## 11.10 Agreements

### 11.10.1 Financing of the trial

The trial is funded by the Federal Ministry for Education and Research (German: BMBF). The general conditions of financing for this trial are addressed in separate agreements.

### 11.10.2 Report

After conclusion of the trial, the sponsor ensures that a report shall be written according to the conditions stipulated in the protocol by. By signing this protocol the investigators agree to disclose their names in the trial report according to § 42b AMG.

### 11.10.3 Publication policy

Any publication of the results, either in part or in total (articles in journals or newspapers, oral presentation, etc.) by the investigators, their representatives, or by the sponsor, shall require the approval of the coordinating investigator.

It is planned to publish the results of the trial as an original article in an appropriate medical journal as well as present at congresses. The coordinating investigator is last author of the article and will present the data at major congresses. The choice of the journal for the publication will be made by the coordinating investigator in agreement with the co-authors. Besides the investigator, further authors of this article have to meet the following criteria:

- Substantial contribution to the recruitment of patients, i.e. one of the five best-recruiting sites within the trial.
- Substantial contribution to the interpretation of the data.
- Substantial contribution to drafting the article or revising it critically for important intellectual content.

## 15 APPENDICES

### 15.1 Additional information regarding inclusion/exclusion criteria

#### Levels of asthma control in children 5 years and younger

**Table 3:** Levels of asthma control as defined by GINA (7)

| Characteristic                                               | Controlled
(all of the following)                                                                                                                      | Partly controlled (any measure
present in any week)                                                                                           | Uncontrolled (three or more of
features of partly controlled
asthma in any week)                                                     |
|--------------------------------------------------------------|-----------------------------------------------------------------------------------------------------------------------------------------------------------|--------------------------------------------------------------------------------------------------------------------------------------------------|--------------------------------------------------------------------------------------------------------------------------------------------|
| Daytime symptoms:
wheezing, cough,
difficult breathing | None (less than twice/week,
typically for short periods
on the order of minutes and
rapidly relieved by use of
a rapid-acting bronchodilator) | More than twice/week (typically
for short periods on the order of
minutes and rapidly relieved by use
of a rapid-acting bronchodilator) | More than twice/week (typically
last minutes or hours or recur, but
partially or fully relieved with
rapid-acting bronchodilator) |
| Limitations of activities                                    | None (child is fully active, plays
and runs without limitation
or symptoms)                                                                         | Any (may cough, wheeze, or have
difficulty breathing during exercise,
vigorous play, or laughing)                                          | Any (may cough, wheeze, or have
difficulty breathing during exercise,
vigorous play, or laughing)                                    |
| Nocturnal symptoms/
awakening                             | None (including no nocturnal
coughing during sleep)                                                                                                    | Any (typically coughs during sleep or
wakes with cough, wheezing, and/
or difficult breathing)                                             | Any (typically coughs during sleep
or wakes with cough, wheezing,
and/or difficult breathing)                                        |
| Need for reliever/
rescue treatment                       | ≤2 days/week                                                                                                                                              | >2 days/week                                                                                                                                     | >2 days/week                                                                                                                               |

This scheme (based on current expert opinion) presents characteristics of controlled, partly controlled, and uncontrolled asthma for children 5 years and younger based on (1) symptoms recognized by family members/caregivers and (2) the child's need for reliever/rescue treatment.

### 15.2 Dosing table systemic corticosteroids

**Table 4:** Dosing recommendations for systemic corticosteroids (Celestamine®)

| Age of patients | Betametasone (mg)        | Betametasone (ml)      |
|-----------------|--------------------------|------------------------|
| 1-2 years       | Twice daily 1.0-1.0 mg   | Twice daily 2.0-2.0 ml |
| 2-3 years       | Twice daily 1.25-1.25 mg | Twice daily 2.5-2.5 ml |
| 3-4 years       | Twice daily 1.5-1.5 mg   | Twice daily 3.0-3.0 ml |
| 3-5 years       | Twice daily 2.0-2.0 mg   | Twice daily 4.0-4.0 ml |

This dose of Betametasone should be given for 3 days during a severe exacerbation

### 15.3 Instructions for the use of the Respimat® inhaler

#### Instructions for Use

Respimat® inhaler

#### How to use your Respimat® inhaler

[figure not shown]

- If Spiriva Respimat has not been used for more than 7 days release one puff towards the ground.
- If Spiriva Respimat has not been used for more than 21 days repeat steps 4 to 6 under 'Prepare for first use' until a cloud is visible. Then repeat steps 4 to 6 three more times.
- Do not touch the piercing element inside the clear base.

### How to care for your Spiriva Respimat

Clean the mouthpiece including the metal part inside the mouthpiece with a damp cloth or tissue only, at least once a week. Any minor discoloration in the mouthpiece does not affect your Spiriva Respimat inhaler performance. If necessary, wipe the outside of your Spiriva Respimat inhaler with a damp cloth.

### When to get a new Spiriva Respimat

[figure not shown]

- Your Spiriva Respimat inhaler contains 60 puffs (30 doses) if used as indicated (two puffs/once daily).
- The dose indicator shows approximately how much medication is left.
- When the dose indicator enters the red area of the scale you need to get a new prescription; there is approximately medication for 7 days left (14 puffs).
- Once the dose indicator reaches the end of the red scale, your Spiriva Respimat locks automatically – no more doses can be released. At this point, the clear base cannot be turned any further.

- Spiriva Respimat should be discarded three months after you have prepared it for first use, even if it has not been fully used or used at all.

### Prepare for first use

|                                                                                                                                                                                                                                                                                                                               |                                                                                      |
|-------------------------------------------------------------------------------------------------------------------------------------------------------------------------------------------------------------------------------------------------------------------------------------------------------------------------------|--------------------------------------------------------------------------------------|
| 
1. Remove clear base
 

• Keep the cap closed.

• Press the safety catch while firmly pulling off the clear base with your other hand.

                                                                                                                      | [figure not shown]   |
| 
2. Insert cartridge
 

• Insert the narrow end of the cartridge into the inhaler.

• Place the inhaler on a firm surface and push down firmly until it clicks into place.

• Do not remove the cartridge once it has been inserted into the inhaler.

 | [figure not shown]   |
| 
3. Replace clear base
 

• Put the clear base back into place until it clicks.

• Do not remove the clear base again.

                                                                                                                                       | [figure not shown] |

|                                                                                                                                                                                                                                                                                                                                                                                                                                                                                                          |                                                                                     |
|----------------------------------------------------------------------------------------------------------------------------------------------------------------------------------------------------------------------------------------------------------------------------------------------------------------------------------------------------------------------------------------------------------------------------------------------------------------------------------------------------------|-------------------------------------------------------------------------------------|
| 
4. Turn
 
 
• Keep the cap closed.
 
• Turn the clear base in the direction of the arrows on the label until it clicks (half a turn).
 
                                                                                                                                                                                                                                                                                                 | [figure not shown]  |
| 
5. Open
 
 
• Open the cap until it snaps fully open.
 
                                                                                                                                                                                                                                                                                                                                                                                        | [figure not shown]  |
| 
6. Press
 
 
• Point the inhaler toward the ground.
 
• Press the dose-release button.
 
• Close the cap.
 
• Repeat steps 4-6 until a cloud is visible.
 
• After a cloud is visible, repeat steps 4-6 three more times.
 
 
Your inhaler is now ready to use. These steps will not affect the number of doses available. After preparation your inhaler will be able to deliver 60 puffs (30 doses).
 | [figure not shown] |

## Daily use

### TURN

- Keep the cap closed.
- **TURN** the clear base in the direction of the arrows on the label until it clicks (half a turn).

[figure not shown]

### OPEN

- **OPEN** the cap until it snaps fully open.

[figure not shown]

### PRESS

- Breathe out slowly and fully.
- Close your lips around the mouthpiece without covering the air vents. Point your Inhaler to the back of your throat.
- While taking a slow, deep breath through your mouth, **PRESS** the dose-release button and continue to breathe in slowly for as long as comfortable.
- Hold your breath for 10 seconds or for as long as comfortable.
- Repeat Turn, Open, Press for a total of 2 puffs.
- Close the cap until you use your inhaler again.

[figure not shown]

## 15.4 Instructions for the use of the Respimat® inhaler with spacer

[figure not shown]

You will need to use this inhaler only **ONCE A DAY**.  
Each time it is used take 1 PUFFS to achieve proper dosing.

[figure not shown]

- I Hold the Respimat® inhaler upright with the cap closed to avoid accidental release of the dose. Turn the clear base in the direction of the red arrows on the label until it clicks (half a turn).

[figure not shown]

- II Open the cap (A) until it snaps fully open

[figure not shown]

- III Now take the spacer.
- Look inside for foreign objects.

[figure not shown]

- IV Insert the mouthpiece of the Respimat® inhaler into the back of the spacer.

[figure not shown]

- V Make sure the nose piece of the spacer and the dose release button are aligned and upright.

Apply the face mask to the face of the child, making sure to obtain a good seal between the face and the spacer

[figure not shown]

- VI When the child starts breathing slowly and steadily, press the dose release button (D).

[figure not shown]

- VII Maintain good seal over your child's mouth and nose for 5 breaths after pressing the dose release button. Take care not to get the spray into the child's eyes.

[figure not shown]

- VIII Pull the spacer and the Respimat® inhaler apart and close the cap of Respimat® inhaler. Now repeat all steps (I–VIII) one more time for a second inhalation to ensure your child receives the full daily dose.

At the completion of the second puff, close the cap until the inhaler is used again.

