| TREATMENTS               | Experimental intervention: Tiotropium 2.5 µg once daily (2 x 1.25 µg; 12 months treatment) via Respimat® inhaler added to ICS (Fluticasone 2 x 50 µg) Control intervention: Placebo Inhaler                                                                                                                                                                                                                                                                                                                                                                                                                                                                                                                                                                                                                                                                                                                                                                                                                                                                                                                                                                                                                                                                                                                                                                                                                                                                                                                                                                                                                                                                                                                                                                                                                                                                                                                                                                                                                                                                                                                     |                   |

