### **Investigations at visit 2**

- V2 will be scheduled 4-6 weeks after V1
- Inclusion/Exclusion criteria
- Physical examination
- Vital signs
- Height and weight
- Previous and concomitant diseases
- Previous and concomitant treatments
- Spirometry/Oscillometry pre and 30 minutes post-dosing in patients  $\geq 4$  years
- Randomization
- Training of Respimat® inhaler with a Respimat® training device with spacer (Appendix 15.4)
- Dispense of study medication
- Dispense/Check of rescue medication
- Download/review TIPP diary App
- Assessment of asthma control according to GINA guidelines
- AEs
- Concomitant therapy

- Drug accountability

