#### When to get a new Respimat® inhaler

[figure not shown]

The Respimat® inhaler contains 30 doses (60 puffs) after priming. The dose indicator shows approximately how many doses are left. When the pointer enters the red area of the scale, there is, approximately, medication for 7 days (14 puffs) left. This is when you need to get a new Respimat® inhaler.

Once the dose indicator has reached the end of the red scale (i.e. all 30 doses have been used), the Respima® inhaler locks automatically. At this point, the base cannot be turned any further.

At the latest, three months after first use the Respimat® inhaler should be discarded even if not all medication has been used.

### What if...

| What if...                                                | Reason                                                                                                                              | What to do                                                                                           |
|-----------------------------------------------------------|-------------------------------------------------------------------------------------------------------------------------------------|------------------------------------------------------------------------------------------------------|
| I cannot turn the base easily.                            | a) The Respimat® inhaler is already prepared and ready to use.

b) The Respimat® inhaler is locked after 60 puffs (30 doses). | a) The Respimat® inhaler can be used as it is.

b) Prepare and use your new Respimat® inhaler. |
| I cannot press the dose release button.                   | The clear base has not been turned.                                                                                                 | Turn the clear base until it clicks (half a turn).                                                   |
| The clear base springs back after I have turned it.       | The clear base was not turned far enough.                                                                                           | Prepare the Respimat® inhaler for use by turning the clear base until it clicks (half a turn).       |
| I can turn the clear base past the point where it clicks. | Either the dose release button has been pressed, or the clear base has been turned too far.                                         | With the gray cap closed, turn the base until it clicks (half a turn).                               |

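### Two appendix dosing instructions are wrong as written: the spacer sheet opens with 1 puff where the dose is 2, and Table 4 lists two betamethasone doses for a 3-year-old (minor, dosing safety)

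*Protocol*

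**What the plan says.** **Inhaler.** The synopsis sets the experimental dose as "Tiotropium 2.5 µg once daily (2 x 1.25 µg; 12 months treatment"), and section 4.1.1 gives the strength as 1.25 µg per actuation. Section 1.3.1 says that all children inhale through a spacer. The visit 2 list in section 5 includes "Training of Respimat® inhaler with a Respimat® training device with spacer (Appendix 15.4"), so Appendix 15.4 is the instruction in use for the whole trial. After stating once-daily use, that appendix opens with "Each time it is used take 1 PUFFS to achieve proper dosing".

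Further down, step VIII says "Now repeat all steps (I–VIII) one more time for a second inhalation to ensure your child receives the full daily dose", and the closing line says "At the completion of the second puff, close the cap until the inhaler is used again". The part on replacing the inhaler says "The Respimat® inhaler contains 30 doses (60 puffs) after priming" and describes the red zone of the indicator as "medication for 7 days (14 puffs) left". Appendix 15.3, for use without a spacer, says "Repeat Turn, Open, Press for a total of 2 puffs".

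**Betamethasone.** Section 7 advises parents to give a three-day oral course in a severe exacerbation, refers to Table 4 and to the manufacturer's directions, and asks for contact with the investigator within 24 hours. Table 4 (Appendix 15.2) has four age rows: 1-2, 2-3, 3-4 and 3-5 years, with 1.0, 1.25, 1.5 and 2.0 mg twice daily. Eligibility in section 3.6.2 runs from 1 year to under 6 at visit 1.

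**The concern.** Both pages carry doses that someone is meant to act on. The wrong figure in Appendix 15.4 stands in the opening dose statement, where a caregiver who already knows the device may stop reading. In Table 4 the overlap leaves a 3-year-old with two listed doses and no rule for choosing between them. The stakes are a halved dose of study medication in any family that follows the opening line alone, and an avoidable ambiguity in a steroid dose for a young child.

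**Working it through.** **Inhaler: inputs.** 1.25 µg per actuation (section 4.1.1); 2.5 µg once daily (synopsis); 60 puffs for 30 doses and 14 puffs for 7 days (Appendix 15.4).

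1. The protocol's own dose, reproduced: 2 puffs × 1.25 µg = 2.5 µg per day.
2. Puffs per dose implied by the inhaler content: 60 / 30 = 2.
3. Puffs per day implied by the red zone: 14 / 7 = 2.
4. Opening line of 15.4: 1 puff × 1.25 µg = 1.25 µg per day, and 1.25 / 2.5 = 50% of the protocol dose. At that rate an inhaler would last 60 / 1 = 60 days instead of 30.

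The synopsis, step VIII, the closing line, both puff counts and Appendix 15.3 agree on two puffs. Only the opening line differs, so it is the error.

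**Table 4: inputs.** The four rows, and the three-day duration in the note under the table.

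| Row (years) | mg, twice daily | ml, twice daily | mg/ml | mg per day | mg over 3 days |
|---|---|---|---|---|---|
| 1-2 | 1.0 | 2.0 | 0.5 | 2.0 | 6.0 |
| 2-3 | 1.25 | 2.5 | 0.5 | 2.5 | 7.5 |
| 3-4 | 1.5 | 3.0 | 0.5 | 3.0 | 9.0 |
| 3-5 | 2.0 | 4.0 | 0.5 | 4.0 | 12.0 |

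1. All four rows give 0.5 mg/ml, so the mg and ml columns are consistent. The likely fault is an age label, not a dose.
2. Read from birthday to birthday, the first three rows do not overlap. The fourth overlaps the third for ages 3 to under 4: 9 or 12 mg over the course, and 12 / 9 − 1 = 33% more in the higher row.
3. On the same reading the last row ends at the fifth birthday, so children aged 5 to under 6 have no row although they are eligible. Relabelling the last row as 4-5 removes the overlap but leaves that gap.
4. If the end ages are read as included, age 3 falls in three rows (1.25, 1.5 and 2.0 mg). That reading is worse, so the overlap does not depend on how the bands are read.

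**The case against.** The strongest reply is that Appendix 15.4 corrects itself. A caregiver who completes the sequence reaches step VIII and gives the second puff. The singular digit with a plural noun looks like a one-character slip, and a reading error in the PDF cannot be fully excluded. Families are trained with a device and spacer at visit 2. Children of 4 years or over who can perform lung function are measured before and 30 minutes after a dose at that visit, so their first dose is taken at the site. All of this stands and keeps the point minor. It does not make the opening line right: a sheet that states two different doses is still defective.

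For Table 4, the reply is that it is headed as recommendations, that section 7 also names the manufacturer's directions, and that the investigator must be contacted. This too stands, and nothing shows that families hold the table. But contact within 24 hours may come after the first dose, and a second reference does not resolve two conflicting rows.

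Three stronger readings are tempting, and the documents do not support them:

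- *A half dose would persist until visit 3.* The first scheduled compliance check is at week 6 ± 1, but nothing in the protocol indicates how long such an error would last.
- *Yearly compliance would still be 93% to 95%.* Half-dosing up to day 49 or day 35 gives 1 − 0.5 × 49 / 364 = 0.933 or 1 − 0.5 × 35 / 364 = 0.952. That is a share of delivered dose and assumes correction at visit 3 with full adherence otherwise. Section 4.1.15 assesses compliance by counting cartridges, which need not give the same figure.
- *A particular age at entry from which a child turns 6 on trial and outgrows Table 4.* This treats the last row as covering all 5-year-olds, whereas placing the overlap at 3 to under 4 reads the rows from birthday to birthday. The cut-off would also move with the screening extension, a repeated or postponed visit 2 and the visit 7 window.

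**Conclusion.** Both instructions are wrong as written, and both are minor matters of dosing safety. The opening line of Appendix 15.4 gives 1.25 µg per day where the protocol requires 2.5 µg. Table 4 gives a child aged 3 to under 4 either 9 or 12 mg of betamethasone over three days. The inhaler finding assumes that the extracted text matches the printed page; nothing in the text suggests otherwise. That the last row of Table 4 was meant to start at 4 years is likely but is an assumption, and the protocol alone cannot settle which dose a 3-year-old should receive.

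A reader might infer a diluted treatment effect or lost power. The documents do not support that: the number of families who would act on the opening line alone is unknown, and the same page corrects it. Nor does the steroid overlap alter the definition of the primary endpoint, which counts hospitalization and days of steroid use, not milligrams.

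**What to change.** 1. Check the opening line of Appendix 15.4 against the source PDF, then change it to 2 puffs once daily.
2. Relabel the age bands of Table 4 so that each eligible age, 1 to under 6, falls in exactly one row. The sponsor should confirm that the last row starts at 4 years and that it covers 5-year-olds.
3. Reissue both pages to the sites and to any families who hold them.

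The cost is two corrected appendix pages and their redistribution. Design, sample size and analysis are unchanged.
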